### Sample size justification

This pilot study is designed to obtain an estimate on the standard deviation of the normalized ankle volume during postoperative recovery and to assess the feasibility of both, the proposed randomized allocation to the treatment arms, and the suggested outcome measures. According to the recommended sample size for feasibility studies, we aim to enroll 25 participants per arm (50 patients in total) [18–21]. This number should be sufficient to allow the determination of variability.

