### Intervention

Patients randomized to either treatment group will receive identical postoperative care, i.e., prescription of analgesics and the classical RICE concept to stimulate resorption of the postoperative swelling. The latter will be initiated right after surgery and continued until discharge from the hospital. Patients are advised to strictly adhere to the RICE concept in order to minimize variability inherent to this type of therapy. In particular, a positioning splint will be placed under the knee and the operated lower leg to elevate the ankle above heart level and ice packs will be provided for cooling during daytime according to the individual preference of the patient. The staff on the ward will not be notified on the treatment arm but asked to record the number of ice packs per day as a surrogate measure of both, the individual preference for cooling and adherence to the baseline therapy. Mobilization during the postoperative period and walking will be allowed with crutches and a lower leg orthosis under partial weight-bearing with 20 kg according to a personal training on a scale under supervision of a physiotherapist and without notification of the physiotherapist on the treatment arm. In patients allocated to RICE^+^, the device-based negative pressure therapy will be initiated on the morning of the 2nd postoperative day by a trained physician/medical student (last year of education) and repeated every 24 h until discharge from the hospital. The first treatment will be right after the wound dressing has been changed to a transparent and sterile film dressing (OPSITE® Post-OP visible, Smith & Nephew Woundcare, Hamburg, Germany). This wound dressing will be applied to all study patients and allow for constant monitoring of the wound and peri-wound area while eliminating the need to remove the dressing every time before the objective evaluation of the edema by 3D scanning and to ensure blinding of the staff with respect to the treatment arm. In all patients scheduled for RICE^+^, negative pressure therapy (30 min per session) will be applied by a trained physician/medical student in a standardized manner, i.e., starting at the supraclavicular fossa and following the lymphatic vessels down to the affected ankle. We use the same sequence as in manual lymphatic drainage, i.e., to increase lymph kinetic in normal lymphatics by mild mechanical stimuli as this augments the drainage across the lymphatic watershed. When starting manual lymphatic treatment at the inflow of the lymph into the venous system, edema fluid will pass through the already dilated area with successive decongestion of the lymphatic trunk [13, 22, 23]. The size of the treatment cup (60–80 mm diameter), the pressure (20–250 mmHg), and the frequency of vibration (20–90 Hz) will be adapted to individual needs (Table 1). To ensure blinding of all persons involved in postoperative care, the person in charge for the device-based negative pressure therapy will show up with the equipment at the pre-defined time anyway.

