Data will be analyzed using the SPSS statistical package 26.0 (SPSS Inc., Chicago, IL) and Sigma Plot V10 (Systat Software GmbH, Erkrath, Germany) for graphical presentation. The normal distribution of continuous variables will be evaluated by the Kolmogorov-Smirnov test, descriptive summary measures will be calculated. Categorical variables are summarized as numbers and percentages. For comparison of the categorical variables, the chi-square test or Fisher’s exact test will be used, as appropriate. Repeated measure analysis will allow for longitudinal examination of the treatment effects and differences between the study groups. Data from all randomized participants will be included (intent-to-treat analysis). No missing data imputation will be performed, and in view of the rather small number of participants per treatment arm, neither subgroup or adjusted analyses are planned. During the study, patients and personnel are encouraged to mention all problems related to the study investigations and especially to the acceptance of the contact-less 3D optical scanning procedure. At the time of discharge, patients randomized to RICE^+^ will be asked by the one in charge for the application of the device-based negative pressure therapy to rate this additional treatment on a scale ranging from 1 (very good) to 5 (no effect). Proceeding to the main trial will be deemed feasible if (a) at least two-thirds of the patients allocated to RICE^+^ will retrospectively judge this additional treatment positive and (b) at least two-thirds of all patients accept the repetitive contact-less 3D optical scanning procedure.

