## Discussion

The study is designed to assess the effects of the classical RICE concept and the additional application of a device-based negative pressure therapy (RICE^+^) with respect to the resorption of lymphedema related to the surgical fixation of an isolated ankle fracture. Although standardization of the components of RICE is hard to achieve even in a hospital setting, we record the number of ice packages per day not only as a marker of the individual preference for cooling but as a surrogate marker of adherence to the baseline therapy, as well. To objectively assess the effects of either therapeutic approach, we decided to perform touchless 3D optical scanning as this turned out to be a highly reliable technique for quantifying the volume of the foot and ankle region [14]. Given the multiple implications of ankle swelling with respect to pain, complications, mobility, and outcome, we selected a rather broad panel of outcome measures covering a 12-week postoperative interval. Although this approach might be prone to any bias related to the RICE concept and/or to the individual care after discharge from the hospital, it will certainly provide data on the immediate effects of RICE vs RICE^+^. The blinding of the evaluator and even the staff involved in surgery and postoperative care and the fact that the person in charge for the device-based application of negative pressure therapy will show up anyway are expected to minimize the risk of a bias in standard care. Further, the dynamics of the ratio of naturally occurring calcium isotopes in relation to the postoperative development of lymphedema, the manifestation of eventual postoperative complications as infection or non-union, and bone mineral density will permit insight into the mechanisms of interaction between perioperative swelling and uneventful bone remineralization or prolonged demineralization in case of complications in the postoperative period. In summary, the results of the proposed pilot study will enable us to decide whether it is worth comparing the effects of RICE and RICE^+^ in a sufficiently powered multicenter trial and which of the outcome markers are best suited for this purpose. Without saying, this decision will consider the feedback of patients on either therapeutic approach as well as comments from the staff.

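### Progression criterion (a) rests on a rating requested by the person who delivered RICE+, with no stated cut-off for 'positive', so a pass would be hard to interpret

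*Protocol article*

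**What the plan says.** The section on data collection, management and statistical analysis gives the progression rule. Proceeding is deemed feasible if two conditions hold:

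- (a) "at least two-thirds of the patients allocated to RICE^+^ will retrospectively judge this additional treatment positive"
- (b) "at least two-thirds of all patients accept the repetitive contact-less 3D optical scanning procedure"

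The sentence just before the rule describes the only patient rating of RICE+ in the article. At discharge, RICE+ patients "will be asked by the one in charge for the application of the device-based negative pressure therapy to rate this additional treatment". Their answer is a score from 1, the best point (very good), to 5, the worst (no effect). The text does not label points 2 to 4, and it does not say which points amount to a positive judgement.

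Under Intervention, the therapy is started "by a trained physician/medical student (last year of education) and repeated every 24 h until discharge from the hospital", with 30 minutes per session. The Sample size justification plans the arm size: "we aim to enroll 25 participants per arm (50 patients in total"). The Discussion adds, on the choice to go on to a multicenter trial, that "this decision will consider the feedback of patients on either therapeutic approach as well as comments from the staff".

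**The concern.** Assessing feasibility is one of the two stated aims of the pilot, and criterion (a) is one of the two conditions in its explicit progression rule. Two features weaken it.

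1. **Who asks.** The rating is requested by the person who has treated the patient every day. Patients may be reluctant to tell that person that the sessions did nothing. Any such reluctance pushes the count towards a pass.
2. **What is counted.** The threshold of two-thirds is fixed, but the event is not. With a five-point score and no cut-off, the same answers can meet or miss the threshold depending on where the line is drawn. Nothing in the text prevents the line from being drawn after the scores have been seen.

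At stake is whether a pass on (a) tells the sponsor that patients valued the treatment. As written, it could equally reflect politeness or a favourable cut-off.

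**Working it through.** **Inputs from the protocol article.** The RICE+ arm has 25 planned patients (Sample size justification). The threshold is two-thirds of those allocated, and the scale runs from 1 to 5 (data collection, management and statistical analysis). The article gives no pass probability or error rate for the rule, so there is no figure of its own to reproduce.

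**Inputs that are assumed.** The distribution of scores and the size of any courtesy effect are not in the document. The values below are illustrations.

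**Step 1: threshold.** 25 × 2/3 = 16.7, so 17 positive ratings are needed (17/25 = 68%).

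**Step 2: chance of passing.** If each patient is positive with probability p, independently, then P(pass) = P(X ≥ 17), with X binomial (25, p).

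| p | P(pass) |
|---|---|
| 0.50 | 0.054 |
| 0.60 | 0.274 |
| 0.667 | 0.538 |
| 0.70 | 0.677 |
| 0.75 | 0.851 |
| 0.80 | 0.953 |

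**Step 3: effect of the cut-off.** For an assumed distribution of scores, p is the share at or below the cut-off.

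| Assumed shares at 1/2/3/4/5 (%) | Cut-off ≤2 | ≤3 | ≤4 |
|---|---|---|---|
| 20/20/20/20/20 | 0.004 | 0.27 | 0.95 |
| 10/20/40/20/10 | 0.0001 | 0.68 | 0.9995 |
| 5/10/20/35/30 | <0.001 | <0.001 | 0.68 |
| 30/35/20/10/5 | 0.47 | 0.99 | >0.99 |
| 5/10/15/20/50 | <0.001 | 0.0001 | 0.054 |

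In the first two rows the cut-off alone takes the result from almost certain failure to almost certain success. In the last row no cut-off up to 4 gives much chance of passing.

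**Step 4: effect of courtesy, with the cut-off held fixed.** Suppose a share s of the patients who are not positive nevertheless answer positively when the operator asks. The observed share is then p + (1 − p)s.

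| True p | s = 0 | 0.1 | 0.2 | 0.3 | 0.5 |
|---|---|---|---|---|---|
| 0.40 | 0.004 | 0.022 | 0.080 | 0.210 | 0.677 |
| 0.50 | 0.054 | 0.134 | 0.274 | 0.467 | 0.851 |
| 0.60 | 0.274 | 0.425 | 0.594 | 0.754 | 0.953 |

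A lift from 60% to 75% corresponds to s = 0.15/0.40 = 0.375 and raises P(pass) from 0.27 to 0.85.

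**Step 5: can the rule fail?** If 9 of 25 patients score 5, at most 25 − 9 = 16 can be positive, which is below 17. The rule then fails at every cut-off up to 4. Only counting 5, the 'no effect' point, as positive would make it pass regardless.

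**The case against.** The best case for the plan has five parts.

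- **The operator is a natural person to ask.** Under Randomization, only the operator and the patient are told the allocation. If ward staff, the physiotherapist or the evaluator asked, they would learn the arm. This stands as a reason not to use those people. It is not a reason to use the operator, because a self-completed form protects the blinding as well.
- **The missing cut-off may be in the full protocol.** Labels for points 2 to 4 may be there, and the article does not expressly tie the score to criterion (a). That is possible. But the article states the decision rule with its threshold and describes no other patient rating of RICE+. Who asks is a stated method, which fuller labels would not change.
- **The scale has no point below 'no effect'.** A reader might infer that this inflates the pass rate. The documents do not support that. Criterion (a) is a count of positive or not, and a patient who felt worse would most naturally choose 5. Complications and discomfort are recorded separately under adverse events reporting, and patients and staff are encouraged to mention problems.
- **The Discussion speaks of feedback on both approaches, while only RICE+ patients give a rating.** A reader might infer a contradiction. There is none: the rating concerns an additional treatment that RICE patients do not receive, and both arms have other routes for comment.
- **The numbers are constructed.** This is true. They show how sensitive the rule is and are no evidence of bias in this trial.

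**Conclusion.** The concern holds in a limited form. Criterion (a) is not fully fixed in advance, and its data are collected in a way that invites courteous answers, so 17 or more of 25 would be hard to interpret. Under an even spread of scores (assumed), the choice of cut-off moves the chance of passing between 0.004 and 0.95. Under an assumed courtesy lift from 60% to 75%, the chance moves from 0.27 to 0.85. Both illustrations assume 25 rated patients and independent answers. Even without these problems the criterion is imprecise: at exactly 17 of 25 the exact 95% confidence interval runs from 46% to 85%.

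A reader might go further and infer that the criterion passes whatever patients think. It does not: nine or more scores of 5 fail it at any cut-off up to 4. Nor does passing (a) start the main trial by itself, since (b) must also be met and the Discussion describes a wider judgement that takes in other feedback. The point is worth correcting because the remedy is cheap and the criterion is half of the stated rule.

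**What to change.** 1. Have RICE+ patients complete the rating themselves at discharge, under the study ID, on a form that neither the operator nor the blinded staff see.
2. State before the first rating is collected which scores count as positive, for example the two best points, and say that this score is what decides criterion (a).
3. Keep all patients allocated to RICE+ in the denominator, as the wording of the criterion already implies, and count a missing rating as not positive. The same section rules out imputation of missing data, so write this as part of the definition: recorded positive ratings divided by all patients allocated to RICE+.

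A balanced scale with points below 'no effect' is optional. It would add descriptive detail but would hardly change the count. Ratings from the RICE arm are not needed for this criterion.

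The cost is a one-page form and a few sentences in the protocol. The pass rate may turn out less favourable.

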**Fig. 1 Fig1:**
[figure not shown]
Study overview *reasons for withdrawl of consent and the number of drop-outs for evaluation of the primary and secondary endopoints are recorded.m

**Table 2 Tab2:** Time schedule of the study examinations

	Screening	The day before surgery	Postoperative period starting day 2			Follow-up (weeks 2, 4, 6)	Final visit (week 12)
			Daily until discharge	Every 2nd day	Discharge		
Inclusion/exclusion criteria	x						
Informed consent	x						
Demographic and medical history	x						
Food Frequency Questionnaire ^17^		x				x^a^	x
Baseline laboratory test^b^		x			x		x
Serum/urine sampling^c^		x		x	x	x	x
Scoring of BMD^d^		x			x		x
Ankle swelling		x	x		x	x	x
Demand for analgesics		x	x		x	x	x
Pain perception (NAS)		x	x		x	x	x
Range of motion					x	x	x
Walking abilities					x	x	x

^a^Part of the follow-up examinations at week 4 only

^b^Routinely performed serum analysis (thyroid hormones, renal and liver function, clotting test, blood cell count) plus the determination of parathyroid hormone, 25-hydroxy vitamin D, total and ionized serum calcium, and phosphate

^c^Determination of δ^44/42^Ca (serum and urine), fetuin-A (serum), and FGF-23 (serum)

^d^Bone mineral density will be scored as normal, osteopenic, or osteoporotic by utilization of quantitative pulse echography (Bindex ®, Bone Index Finland Ltd., Kuopio, Finland)

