### Adverse events reporting and data safety monitoring

This is a single-center evaluator blinded randomized controlled pilot study, and the device-based application of negative pressure therapy is deemed to be of rather low risk. The same holds true for the proposed outcome measures, i.e., chart review, questionnaires, and touchless 3D optical scanning of the ankle and lower leg. However, all complications (e.g., wound-healing problems, infections) are to be recorded, and participants will be encouraged to report any discomfort related to either therapy or outcome measures. Discontinuation or modification of the treatment will be an individual decision of the responsible physician. There will be no special criterion for stopping the trial except for severe postoperative complications making a surgical reintervention necessary.

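### Go/no-go criterion (b) needs an accept / not accept value for every patient, but the plan does not define acceptance of the 3D scan and describes only encouraged reporting of problems as its source

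*Protocol article*

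**What the plan says.** The section on data collection, management and statistical analysis sets two conditions for going on to the main trial. Condition (a) concerns how RICE+ patients judge the suction treatment. Condition (b) is that "at least two-thirds of all patients accept the repetitive contact-less 3D optical scanning procedure".

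On how scan acceptance becomes known, the same section says that "patients and personnel are encouraged to mention all problems related to the study investigations and especially to the acceptance of the contact-less 3D optical scanning". The section on adverse events adds that "participants will be encouraged to report any discomfort related to either therapy or outcome measures".

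For condition (a) the article is more specific. At discharge, the person applying the negative pressure asks each RICE+ patient for a rating from 1 to 5. That rating goes to one arm only and concerns the treatment, not the scan.

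The planned size is 25 per arm, 50 in total (Sample size justification). Table 2, "Time schedule of the study examinations", lists ankle swelling, which is the scan, on the day before surgery, daily until discharge, at discharge, at weeks 2, 4 and 6, and at week 12. It has no row for scan acceptance. The note to Fig. 1 says that reasons for withdrawal and "the number of drop-outs for evaluation of the primary and secondary endopoints are recorded".

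**The concern.** Condition (b) is a proportion with all patients as the denominator. Encouraging people to mention problems produces a list of complaints. It does not produce a yes or no for each of 50 patients, and the article does not say how a patient without a complaint is classified.

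Assessing the feasibility of the outcome measures is one of the pilot's two stated aims, and the scan supplies the primary outcome. Condition (b) is the only part of the progression rule that concerns the scan. Several ways of counting are open: absence of complaint, completion of scans, or absence of withdrawal. They can give different go/no-go answers, and the choice could be made after the data are seen. The most direct use of the described source, treating no complaint as acceptance, biases the share upward.

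**Working it through.** **What there is to reproduce.** The article gives no count, error rate or operating characteristic for condition (b). The figures below are therefore an illustration, not a check of a stated number.

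**Inputs from the document.** n = 50; threshold two-thirds of all patients.

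**Threshold as a count.** 50 × 2/3 = 33.3, so at least 34 acceptors are needed. The criterion fails only with 50 − 33 = 17 or more non-acceptors.

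**Assumptions, not in the document.**
- p: true share of patients who accept the scans.
- s: share of non-accepting patients who say so when merely encouraged to mention problems.
- A patient with no reported problem is counted as accepting. This is one possible reading; the document states no rule.
- Patients are independent.

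**Formulas.** Apparent acceptance is q = 1 − (1 − p) × s. The chance of passing is P(X ≥ 34) with X binomial(50, q). If everyone is asked, s = 1 and q = p.

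Example: p = 0.50 and s = 0.50 give q = 1 − 0.50 × 0.50 = 0.75 and P(X ≥ 34) = 0.902. With everyone asked, q = 0.50 and P(X ≥ 34) = 0.008.

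**Chance of passing:**

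| True acceptance p | All asked (s = 1) | s = 0.75 | s = 0.50 | s = 0.25 |
|---|---|---|---|---|
| 0.40 | 0.000 | 0.043 | 0.684 | 0.999 |
| 0.50 | 0.008 | 0.258 | 0.902 | 1.000 |
| 0.60 | 0.156 | 0.684 | 0.986 | 1.000 |
| 0.70 | 0.684 | 0.958 | 0.999 | 1.000 |
| 0.80 | 0.986 | 0.999 | 1.000 | 1.000 |

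**Why the values move so fast.** At p = 0.50 about 25 patients object. If half speak up, 12.5 complaints are expected, below the 17 needed to fail. If three-quarters speak up, 18.75 are expected, just above 17, and the criterion usually fails as it should. At p = 0.80 only 10 patients object, so the criterion nearly always passes however the information is gathered.

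**The case against.** The strongest case on the other side has five parts.

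1. **Acceptance may be meant behaviourally.** Scans are scheduled for every patient, missed ones would show in the primary-outcome data, and withdrawals and drop-outs are recorded. A reader might infer that silence counts as acceptance and that no data bear on the criterion at all. The documents support neither: they give no rule for silence, and usable data would exist. What remains is that the article does not link those data to condition (b).

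2. **The absence from Table 2 proves little.** The table also has no row for the RICE+ rating or for complications, and both are collected. This stands, and the point does not rest on Table 2.

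3. **A journal article leaves forms and item wording to the full protocol.** That is true in general. Here, however, the same section states the instrument for (a) and, for scan acceptance, states a method that cannot yield the required proportion. That is a mismatch between two stated things, not only an omitted detail.

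4. **The reporting is prompted.** Patients and staff are both encouraged to speak, and scan acceptance is singled out. This stands, and it argues for a higher speak-up share. A reader might infer that the criterion passes almost by default. The table supports that only where true acceptance is already high or about half or more of objectors stay silent. For a touchless procedure that the article regards as low risk, true acceptance may well be high, and then the method changes little.

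5. **The decision is not mechanical.** The Discussion says that feedback from patients on either therapeutic approach and comments from staff will be considered. That softens the consequence. It does not supply the count that (b) requires.

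**Conclusion.** The point holds in a limited form. Condition (b) requires 34 of 50 patients to accept repeated scanning. The article does not define acceptance, describes only encouraged problem reports as its source, and does not connect scan completion or withdrawal to it. One of the two progression conditions therefore cannot be evaluated unambiguously as written.

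The size depends on how silence is read and on two quantities the documents do not give. If silence is read as acceptance and true acceptance is 50%, the chance of passing rises from 0.8% to 26%, 90% or about 100% as the speak-up share falls from 75% to 50% to 25%. At 60% it rises from 16% to 68%, 99% or about 100%. At 80% it is 98.6% even with everyone asked, so the defect would rarely change the decision. The change is worth making because it is cheap and removes a choice that could otherwise be made after the results are known.

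**What to change.** At discharge, put one fixed yes/no question on acceptance of the repeated scans to every patient in both arms. Use a self-completed form that the scan evaluator does not administer, and base condition (b) on that answer.

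State the counting rules in advance:
- Refusal of scans, or withdrawal because of scanning, counts as not accepting.
- Patients with no answer for other reasons are reported separately, not scored as rejecting the scan. A sensitivity count shows whether the decision would change if they were all counted as not accepting (34 of 50 needed). If, say, 45 patients have a value, two-thirds of them is 30.
- The share of scheduled scans completed is reported alongside as a description. This also covers the scans at weeks 2 to 12, which a discharge question cannot.
- The two-thirds threshold stays.

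The cost is one form item at an existing time point and a tally of completed scans. The reported acceptance share will probably be lower than one built on problem reports.
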